## Abstract

**Background:**

Current guidelines recommend dual anti-platelet therapy, aspirin and clopidogrel, for patients treated with drug-eluting stent for coronary heart disease. In a few small trials, addition of cilostazol on dual anti-platelet therapy (triple anti-platelet therapy) showed better late luminal loss. In the real-world unselected patients with coronary heart disease, however, the effect of cilostazol on platelet reactivity and ischemic vascular events after drug-eluting stent implantation has not been tested. It is also controversial whether there is a significant interaction between lipophilic statin and clopidogrel.

**Methods/Design:**

CILON-T trial was a prospective, randomized, open-label, multi-center, near-all-comer trial to demonstrate the superiority of triple anti-platelet therapy to dual anti-platelet therapy in reducing 6 months' major adverse cardiovascular/cerebrovascular events, composite of cardiac death, nonfatal myocardial infarction, target lesion revascularization and ischemic stroke. It also tested whether triple anti-platelet therapy is superior to dual anti-platelet therapy in inhibiting platelet reactivity in patients receiving percutaneous coronary intervention with drug-eluting stent. Total 960 patients were randomized to receive either dual anti-platelet therapy or triple anti-platelet therapy for 6 months and also, randomly stratified to either lipophilic statin (atorvastatin) or non-lipophilic statin (rosuvastatin) indefinitely. Secondary endpoints included all components of major adverse cardiovascular/cerebrovascular events, platelet reactivity as assessed by VerifyNow P2Y12 assay, effect of statin on major adverse cardiovascular/cerebrovascular events, bleeding complications, and albumin-to-creatinine ratio to test the nephroprotective effect of cilostazol. Major adverse cardiovascular/cerebrovascular events will also be checked at 1, 2, and 3 years to test the 'legacy' effect of triple anti-platelet therapy that was prescribed for only 6 months after percutaneous coronary intervention.

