### Randomization and interventions

All patients received 300 mg aspirin and 300~600 mg clopidogrel loading before the procedure unless the patient had been taking these medications for at least 1 week before the procedure. Patients were randomized to receive either conventional DAT or TAT and also, randomly stratified to take equipotent doses of either atorvastatin 20 mg or rosuvastatin 10 mg per day before the interventional procedure. The patients were also stratified according to the enrolling medical centers/hospitals. A loading dose of cilostazol (Otsuka Korea) 200 mg was given immediately before the procedure. Random allocation of the patients was done via a Web-based computerized program separately managed at medical research collaboration center, Seoul National University Hospital. PCI was done according to the standard technique and the decision of the pre-dilatation and use of glycoprotein IIb/IIIa inhibitors were up to the operator's discretion. The target lesion/vessel was designated as the first lesion/vessel that was intervened. Platelet reactivity was measured by using the Ultegra Rapid Platelet Function Assay (VerifyNow^® ^Aspirin and VerifyNow^® ^P2Y12 assay, Accumetrics Inc., San Diego, California, USA) immediately before discharge.

After enrollment and index PCI procedure, clinical follow-up was planned at 1, 3, 6 months and all patients were recommended follow-up coronary angiography at 6 months according to local clinical practice. Platelet reactivity was also measured at 6 months after index procedure. The investigators were urged to follow the patients, either by office visits or by telephone contacts as necessary. Patient adherence to the study drug was checked at every outpatient visit and the decision of the drug discontinuation was always discussed and checked under the physician's recommendation.

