### Outcome measures

The primary endpoint of this study was the rate of MACCE, a composite ischemic vascular event following PCI, including cardiac death, nonfatal MI, TLR and ischemic stroke at 6 months in the DAT and TAT group. The key secondary endpoints defined a priori are

- P2Y12 reaction unit (PRU) as assessed by VerifyNow^® ^P2Y12 assay

- Cardiac death, nonfatal MI, TLR, target vessel revascularization (TVR), stent thrombosis and ischemic stroke

- MACCE according to the type of statin and its interaction with clopidogrel

- Bleeding, as defined according to the TIMI bleeding classifications [22], major bleeding defined by the presence of at least 1 of the following: intracranial bleeding (documented with magnetic resonance imaging, computed tomography, any other examination or autopsy), or clinically overt bleeding resulting in a 5 g/dL decrease in hemoglobin value (or, when hemoglobin values were not available, a 15% decrease in hematocrit).

- Angiographic outcome, such as late luminal loss, binary restenosis at 6 months' follow-up angiography

- Albumin-to-creatinine ratio

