### Statistical Analysis

#### Sample size calculation

To test the hypothesis that TAT is superior to DAT in reducing MACCE at 6 months after PCI, based on the previous outcome data [10,13,23], we assumed that MACCE rate in DAT and TAT group would be 10% and 5% respectively. Using a superiority design, an estimated total of 960 patients was needed to ensure a power of at least 80% to detect a 5% difference in the composite of ischemic vascular events between the two anti-platelet therapy groups using a two-sided t-test, with a sampling ratio of DAT:TAT at 1:1, bilateral risk set at 5% and drop-out rate estimated to be 10%.

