#### Statistical Analyses

All analysis will be done by intention-to-treat method (all patients analyzed as part of their assigned treatment group). However, per protocol (patients analyzed as part of their assigned group only if they actually received their assigned treatment) and as-treated analysis will also be performed solely for descriptive comparison.

The primary endpoint of 6 months' MACCE will be analyzed using χ^2^-test on an intention-to-treat analysis. The hypothesis will be evaluated based on a superiority testing. The clinical secondary endpoints will also be tested based on χ^2^-test, similarly as primary endpoint testing. The endpoints will be analyzed in pre-specified subgroups, which includes the presence of diabetes mellitus, long lesions (lesion length≥28 mm), small vessel lesions (lesion diameter < 2.75 mm), age and sex. Also, most importantly, post-hoc analysis of MACCE according to the type of statin given (atorvastatin vs. rosuvastatin) will be done. Analysis of platelet function will be tested using repeated ANOVA method with the Bonferroni's correction.

Continuous variables will be presented as mean ± SD and compared with the use of unpaired Student's t-test or in the case of non-normal distribution, Mann-Whitney U test. Categorical variables will be summarized as number or percentages and compared with χ^2 ^or Fisher's exact test, as appropriate. Survival curves using all available follow-up data will also be constructed for time-to-event variables using Kaplan-Meier estimates and compared by log-rank test. A p-value < 0.05 will be considered statistically significant.

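### MACCE at 1, 2 and 3 years, with no split at 6 months, can show that an early difference is retained, but not that there is a legacy effect after cilostazol stops

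*Protocol article*

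**What the plan says.** The long-term aim is stated as a test in the Methods/Design part of the Abstract: "Major adverse cardiovascular/cerebrovascular events will also be checked at 1, 2, and 3 years to test the 'legacy' effect of triple anti-platelet therapy", with the qualifier "that was prescribed for only 6 months after percutaneous coronary intervention". The Background puts the long-term question more loosely, as whether the effects persist. Legacy is not defined anywhere in the article.

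On method, Statistical Analyses assigns the chi-square test to 6-month MACCE and to the clinical secondary endpoints. It then adds: "Survival curves using all available follow-up data will also be constructed for time-to-event variables using Kaplan-Meier estimates", compared by log-rank test. No landmark and no split of follow-up at 6 months is mentioned.

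The primary endpoint in Outcome measures is the MACCE rate following PCI, "including cardiac death, nonfatal MI, TLR and ischemic stroke at 6 months in the DAT and TAT group". MACCE at a stated time is thus used for events from the procedure up to that time.

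**The concern.** The randomised treatments differ for 6 months. The natural meaning of a legacy effect is what the earlier treatment does to events after it has stopped. A curve or rate that starts at the index procedure counts every on-treatment event again at 1, 2 and 3 years.

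If the primary hypothesis is true, the arms already differ at 6 months. They will still differ later, even when cilostazol does nothing after it is stopped. The long-term comparison would then largely repeat the primary result, and a significant result could be reported as a lasting drug effect that the data do not show.

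**Working it through.** **Inputs from the article (Sample size calculation).** "we assumed that MACCE rate in DAT and TAT group would be 10% and 5% respectively" at 6 months; 960 patients, 1:1, so 480 per arm; two-sided 5%; power at least 80%; 10% drop-out, so 480 × 0.90 = 432 per arm.

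**Reproducing the plan's figure.** Two proportions with unpooled variance: n = (1.960 + 0.842)² × (0.10×0.90 + 0.05×0.95) / 0.05² = 431.7, so 432 per arm. Then 432 / 0.90 = 480 per arm, or 960 in total. The stated sample size is reproduced exactly.

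**Assumption not in the article.** After month 6 the hazard λ is the same in both arms, between 2% and 5% per year. The true post-treatment effect is therefore zero.

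**Cumulative rates.** With r(t) = 1 − exp(−λ(t − 0.5)):
- DAT: 0.10 + 0.90·r(t)
- TAT: 0.05 + 0.95·r(t)
- Difference: 0.05·(1 − r(t)), so the early gap shrinks only slowly.

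**Chance of a significant cumulative comparison.** Φ[(d − 1.96·se0)/se1], where d is the difference, se0 the pooled and se1 the unpooled standard error. The two-proportion test is used here as a simple stand-in for a comparison that counts all events from the procedure; it is not a log-rank calculation.

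Worked case, 1 year, λ = 0.02, 480 per arm: r = 0.00995; DAT 10.9%, TAT 5.9%; d = 0.0495; se0 = 0.01792; se1 = 0.01785. Then (0.0495 − 1.96 × 0.01792)/0.01785 = 0.80, and Φ = 0.79.

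| Time | DAT, λ 2% to 5% | TAT, λ 2% to 5% | Significant, 480/arm | Significant, 432/arm |
|---|---|---|---|---|
| 1 year | 10.9% to 12.2% | 5.9% to 7.3% | 79% to 72% | 75% to 68% |
| 2 years | 12.7% to 16.5% | 7.8% to 11.9% | 70% to 54% | 65% to 50% |
| 3 years | 14.4% to 20.6% | 9.6% to 16.2% | 62% to 42% | 58% to 39% |

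**Check by simulation.** 200,000 trials were run for each post-6-month risk r of 2%, 5%, 10% and 15%, equal in both arms. The cumulative chi-square rejected in 75%, 62%, 46% and 36% of trials at 480 per arm, and in 70%, 58%, 43% and 33% at 432 per arm. A chi-square on later events only, in patients event-free at 6 months, rejected in 4.9% to 5.0% throughout.

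**The case against.** - **Legacy may simply mean persistence.** The Background wording allows this. If the question is whether patients given 6 months of triple therapy are better off at 3 years, the cumulative comparison by randomised arm answers it and keeps the randomisation. This stands. The rejections above detect a real difference in cumulative MACCE; they mislead only if read as an effect after stopping. It is why the term needs a definition.
- **The method is not tied to the legacy question.** A reader might infer that the plan tests the 1- to 3-year rates by chi-square. It does not say so: chi-square is assigned to 6-month MACCE and the clinical secondary endpoints, and neither Outcome measures nor Appendix 1 lists MACCE at 1, 2 and 3 years. The Kaplan-Meier and log-rank sentence is general and is not named as the legacy test. A landmark may exist in a document not shown. What remains is that the article names a measure for the legacy effect, and on its plain reading that measure does not isolate one.
- **A late rebound would be hidden.** A reader might infer this too. With a TAT hazard 25% higher after stopping (assumed), 3-year rates would still favour TAT, at 14.4% versus 10.8% for λ = 2% or 20.6% versus 18.7% for λ = 5%. A single late rate could mask that, but the planned curves would show the arms converging, so the stronger claim is not supported.
- **The follow-up schedule contradicts the aim.** Randomization and interventions says "After enrollment and index PCI procedure, clinical follow-up was planned at 1, 3, 6 months" and gives no yearly contacts. In a condensed article that is an omission, not a contradiction with the Abstract.
- **A landmark set is not randomised.** Correct. The 5% error rate of the landmark test assumes equal later risk among patients who reach 6 months event-free, and selection can disturb that.

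**Conclusion.** The point holds in a limited form. As stated, the long-term comparison can show whether a 6-month difference is retained, but cannot separate that from an effect after cilostazol stops. With no post-treatment effect it would be significant in about 42% to 79% of trials at 480 per arm, or 39% to 75% at 432 per arm.

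Those figures rest on three assumptions: the full 10% versus 5% difference is real, later hazards are equal at 2% to 5% per year, and the stated number per arm is followed to each time point. Without a 6-month difference the problem does not arise. The documents do not show that the trial would report a false legacy effect, only that the stated comparison leaves room for it. The primary endpoint, its test and the sample size are unaffected. Priority is low to moderate.

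**What to change.** 1. State what legacy means: retention of the early difference, an effect on events after month 6, or both.
2. Keep the cumulative 1-, 2- and 3-year comparison by randomised arm, labelled as the overall outcome.
3. Add a supportive landmark analysis of first MACCE after the close of the 6-month visit window, by randomised arm, in patients alive, MACCE-free and still in follow-up at that point. Follow-up angiography is recommended at 6 months, so placing the cut after the window keeps the TLR it prompts in the first period.
4. Show the hazard ratios for 0 to 6 months and after 6 months side by side.

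The cost is analysis wording only, on data already due to be collected. The downside is that the landmark set is selected after randomisation, so it should be labelled supportive and read together with the cumulative curves.

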**Discussion:**

CILON-T trial will give powerful insight into whether triple anti-platelet therapy is superior to dual anti-platelet therapy in reducing ischemic events and platelet reactivity in the real-world unselected patients treated with drug-eluting stent for coronary heart disease. Also, it will verify the laboratory and clinical significance of drug interaction between lipophilic statin and clopidogrel.

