Additionally, there have been numerous questions as to whether there are significant interaction between clopidogrel and lipophilic statin and whether such interaction can be overcome by the addition of cilostazol. Although data on this matter is controversial but somewhat been in favor of being no significant in vivo interaction between clopidogrel and lipophilic statin [15], the interpretation and application of these data have been restricted by the unrandomized/unstratified manner of the studies [16-18] and non-prospective collection of the data [19]. Also, although the pleiotrophic effect of cilostazol in renal function has been demonstrated in some animal experiments [20,21], whether this holds true for humans have never been investigated.

In order to provide a definite answer to the above questions, we planned the 'Influence of **CIL**ostazol-based triple anti-platelet therapy **ON **Ischemic Complication after drug-eluting sten**T **implantation (**CILON-T**)' study. In this study, we compared the efficacy and safety of triple anti-platelet therapy (TAT), composed of aspirin, clopidogrel and cilostazol, with the conventional DAT by evaluating MACCE and platelet reactivity in an unselected population of patients receiving PCI with DES for coronary heart disease (CHD) in real-world practice. In addition, we would like to get answers for the issues whether lipophilic statin-clopidogrel interaction would influence the patient outcome and whether cilostazol can overcome such interaction, using atorvastatin (Lipitor^®^, Pfizer) dependent on cytochrome P450-3A4 (CYP3A4) for metabolism versus rosuvastatin (Crestor^®^, AstraZeneca) independent from CYP3A4.

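### On MACCE the trial cannot verify a statin-clopidogrel interaction: all patients take clopidogrel, so only a statin comparison and a low-powered cilostazol-by-statin interaction can be estimated

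*Protocol article*

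**What the plan says.** The Discussion paragraph of the abstract states that "it will verify the laboratory and clinical significance of drug interaction between lipophilic statin and clopidogrel". The Background promises a definite answer to a set of questions and lists among the trial's aims "whether lipophilic statin-clopidogrel interaction would influence the patient outcome and whether cilostazol can overcome such interaction". Outcome measures, under key secondary endpoints defined a priori, lists "MACCE according to the type of statin and its interaction with clopidogrel"; Appendix 1 repeats it.

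Randomization and interventions states that "All patients received 300 mg aspirin and 300~600 mg clopidogrel loading before the procedure", with an exception for patients already taking these drugs. The Background defines TAT as aspirin, clopidogrel and cilostazol, against conventional DAT. Statin type (atorvastatin or rosuvastatin, at doses called equipotent) is the second randomised factor. Platelet reactivity is measured before discharge and at 6 months.

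Sample size calculation addresses DAT versus TAT only: "we assumed that MACCE rate in DAT and TAT group would be 10% and 5% respectively", and "an estimated total of 960 patients was needed to ensure a power of at least 80% to detect a 5% difference". No power is stated for any statin contrast. Statistical Analyses plans a comparison of MACCE by statin type and labels it post-hoc. It analyses platelet function by repeated ANOVA with Bonferroni correction, without naming the factors. The later section on issues sought in the trial is more modest: there the data are expected to add information on the clopidogrel-statin question.

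**The concern.** To show on MACCE that a statin changes the effect of clopidogrel, one needs the statin contrast both with and without clopidogrel. Every patient here receives it. A MACCE difference between the statin groups would combine any interference with clopidogrel and any other difference between the two drugs, and nothing in the design separates them. This is a matter of what can be identified, so no analysis detail elsewhere could repair it.

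The interaction that can be estimated, cilostazol by statin, is the nearest the trial comes to asking whether cilostazol overcomes the effect. It was not part of the sample size.

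At stake is what the trial may conclude. A null MACCE result by statin would be weak evidence of no interaction, and a positive one would not establish that clopidogrel was involved. The article also faults earlier clinical evidence for being observational or post-hoc, then gives its own statin analysis the post-hoc label although the endpoint is listed as a priori.

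**Working it through.** **1. The plan's own figure.** Inputs from Sample size calculation: 10% versus 5%, two-sided 5%, 80% power, 1:1, 10% drop-out, "using a two-sided t-test". With unpooled binomial variances:

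n per arm = (1.960 + 0.842)² × (0.10×0.90 + 0.05×0.95) / 0.05² = 7.849 × 0.1375 / 0.0025 ≈ 432.

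432 / 0.90 = 480 per arm, or 960 in total. The stated size reproduces exactly, for DAT versus TAT.

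**2. Assumptions for the statin contrasts (not in the article).** Statin allocation 1:1, giving 960/4 = 240 per cell, or 216 after 10% drop-out. Illustrative MACCE rates: DAT+atorvastatin 12.5%, DAT+rosuvastatin 7.5%, and 5% in both TAT cells. These average to the planned 10% and 5%. The interaction is 5 points, as large as the planned main effect.

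**3. Cilostazol-by-statin interaction on MACCE.** Power = Φ(|δ|/SE − 1.96) + Φ(−|δ|/SE − 1.96).

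*Risk difference.* SE = √[Σp(1−p)/n], with Σp(1−p) = 0.1094 + 0.0694 + 0.0475 + 0.0475 = 0.2738.
- n = 240: SE = 0.0338, δ/SE = 1.48, power 32%.
- n = 216: SE = 0.0356, δ/SE = 1.40, power 29%.

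The SE for DAT versus TAT with 480 per arm is √(0.1375/480) = 0.0169, half that of the interaction.

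*Log-odds.* δ = logit(0.125) − logit(0.075) = 0.566; SE = √[Σ1/(n p(1−p))].
- n = 240: SE = 0.523, power 19%.
- n = 216: SE = 0.551, power 18%.

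The total N for 80% power is about 3,440 (risk difference) or 6,430 (log-odds). A 10-point interaction (15/5/5/5%) has 85% power at 240 per cell and 81% at 216 on the risk-difference scale. A 2-point interaction (11/9/5/5%) has 7-9% across both scales and both cell sizes.

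**4. Statin contrast on MACCE (two-proportion test, assumed rates).**

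| Contrast | Full numbers | After 10% drop-out |
|---|---|---|
| 9% vs 6%, all patients (480 or 432 per group) | 42% | 39% |
| 8.5% vs 6.5%, all patients | 22% | 20% |
| 12.5% vs 7.5%, DAT only (240 or 216 per group) | 45% | 41% |

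Around the 7.5% average rate, 80% power needs a statin gap of about 4.8 to 5.0 points.

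**5. Laboratory side.** The article gives no SD for PRU; 60 to 100 is assumed. The difference detectable with 80% power is SD × √(2/n) × 2.802.
- Statin difference, 480 per group, SD 60: 10.9 PRU. With 432 per group, SD 100: 19.1 PRU.
- If only 60% have a reading (288 per group): 14.0 to 23.3 PRU.
- Cilostazol-by-statin interaction on PRU, full data: twice the first range, about 22 to 38 PRU.

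**The case against.** The strongest reply is that the interaction is meant pharmacologically. The Background frames it as CYP3A4-dependent atorvastatin against CYP3A4-independent rosuvastatin. Randomising clopidogrel-treated patients between them, with a P2Y12 assay as readout, is a direct way to ask whether the lipophilic statin weakens clopidogrel. This stands for PRU. The evidence remains indirect, because no reading off clopidogrel is described. It does not carry over to MACCE, which is not specific to clopidogrel's action; equipotent dosing removes only one difference between the statins.

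A reader might infer that the whole claim, laboratory half included, is beyond the design. The documents do not support that: statin type is randomised and PRU is measured twice on clopidogrel. Nor do they show that PRU would go unused for this question. The article names a by-statin analysis only for MACCE, but its ANOVA plan does not list its factors, and such detail may sit in the full plan.

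It is also fair to say that low power for a secondary endpoint is not an error, that no statin power is claimed, and that the article elsewhere uses modest wording. The power figures therefore serve only to show that the clinical claims are too strong. Finally, the article presents clopidogrel-containing dual therapy as required after drug-eluting stents, so this point does not ask for a clopidogrel-free group.

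**Conclusion.** The concern holds for the clinical half of the claim. With clopidogrel in both arms, the a priori MACCE endpoint cannot deliver a statin-clopidogrel interaction. It delivers a statin comparison in clopidogrel-treated patients and a cilostazol-by-statin interaction. The latter has roughly 18-32% power for an effect as large as the planned main effect, depending on scale and drop-out; a 9% versus 6% statin effect has 39-42%. These figures rest on assumed 1:1 statin allocation and assumed rates. The identification problem rests on neither.

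The laboratory half is within reach as an indirect comparison, with precision that depends on the assumed PRU SD. The a priori and post-hoc labels for the statin analysis contradict each other. The primary DAT versus TAT comparison and its sample size are unaffected.

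**What to change.** - Restate the endpoint in Outcome measures and Appendix 1, and the claims in the abstract and Background, as atorvastatin versus rosuvastatin in clopidogrel-treated patients. This matches the more modest section on issues sought in the trial. For clinical outcome, drop the words *verify* and *definite answer*.
- Reconcile the a priori label in Outcome measures with the post-hoc label in Statistical Analyses.
- Name PRU by randomised statin, with the antiplatelet-by-statin term, as the pre-specified test of the pharmacologic question.
- Report MACCE by statin, and its interaction with cilostazol, as estimates with 95% confidence intervals. State the scale and the limited power, with its assumptions.

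The cost is wording and one model on data already collected. No further patients or measurements are needed. The downside is a more modest stated claim.
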